#### Secondary endpoints

Clinical PFS: time between randomization and the appearance of a new recurrence (any N1 or M1) as suggested by PET-CT or PET-MRI, symptoms related to progressive PCa or death due to any cause.Local recurrence: evidence of a recurrence on imaging inside the surgical or radiotherapy field. Confirmation per biopsy is recommended. For radiotherapy schedules, local response and local progression is defined as per RECIST 1.1 criteria.Regional nodal recurrence: radiographic evidence (PET-CT or -MRI) of lymphadenopathy in the pelvis, outside the surgical or radiotherapy field. Histologic confirmation is recommended, especially in the absence of biochemical recurrence.Distant recurrence: appearance of distant metastases (M1a, M1b, M1c) outside the pelvis evidenced by PET-CT or -MRI.Biochemical PFS: time between randomization and the day of the first recorded biochemical progression (as defined below), clinical progression or death due to clinical progression.RP at diagnosis: biochemical recurrence = PSA > 0.20 ng/mL, confirmed 2 weeks later.Prostate radiotherapy at diagnosis: biochemical recurrence = PSA nadir + 2 ng/mL (Phoenix definition).Patients whose PSA does not drop below 0.20 ng/mL (if previous RP) or below the level before treatment (if previous prostate radiotherapy) at time of first response assessment at 3 months follow-up, are considered as non-responders to treatment and are considered to have a biochemical recurrence in case a second measurement at least 2 weeks later confirms a stable or rising PSA above this level.Time to start of hormonal treatment: time from trial randomization to start of hormonal treatment.Time to castration-resistant disease: time from trial randomization until castration resistant status as defined in the EAU-guidelines [1].PCa-specific survival: time from trial randomization until death due to PCa.Overall survival (OS): time from trial randomization until death from any cause.Acute and late toxicity due to radiotherapy will be assessed according to the National Cancer Institute Common Terminology Criteria for Adverse Events (CTCAE) version 4.0 [20], with special attention for rectal, gastro-intestinal and urinary adverse events. Surgery related morbidity, e.g. intra-operative complications (blood loss, injury to other pelvic organs …), and post-operative surgical complications will be scored using the Clavien-Dindo Classification of Surgical Complications [21].Acute toxicity: occurring during and up to 3 months after treatment completion.Late toxicity: occurring later than 3 months after treatment completion.Quality of life (QoL) scoring using the EORTC QLQ-C30 supplemented with QLQ-PR25. Raw scores will be transformed to a linear scale ranging from 0 to 100 according to the EORTC manual. The multi-item scales of the QLQ PR-25 will be analysed at both the individual item and the scale level. The results will be presented in accordance with recent guidelines for reporting health related QoL randomized controlled trials [22].Pattern of progression.Sensitivity/specificity of PET-imaging for the detection of nodal recurrences: limited to patients undergoing surgery.Biomarker discovery: to develop a miRNA panel predictive for treatment response using whole genome miRNA expression profiling [23].

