**Quality of life**										
QLQ-C30		x						x	x	x
QLQ-PR25		x						x	x	x
**Survival status**							x	x	x	x

(a) All arms should receive an LHRH-agonist or antagonist for a duration of 6 months using 1 monthly formulations. In case of SBRT/WPRT, ADT should start no later than the first fraction (whichever RT treatment comes first) and no earlier than 2 weeks before the start of radiotherapy. In case of sLND, ADT should be started no earlier than 1 day postoperatively and no later than 10 days postoperatively

(b) Treatment should start preferably within 4 weeks after randomization, but no later than 8 weeks after randomization. Treatment period is defined as the time between first treatment day and last treatment of surgery and/or radiotherapy

(c) Physical examination including scoring of Performance Status. Weight and height will only be measured at screening

(d) Whole body choline, PSMA or FACBC PET-CT/−MRI. During follow-up repeat PET-CT only at time of biochemical relapse and then 6-monthly afterwards until clinical progression is determined or earlier in case of symptomatic progression

(e) Optional: for patients without a prior radical prostatectomy it is recommended to perform a multiparametric MRI of the prostate to rule out local recurrence

(f) During the treatment period a toxicity assessment should be done at least once a week in case of WPRT. For SBRT toxicity assessment should be done only at end of treatment, for sLND at discharge (Clavien-Dindo scale)

(g) 6-monthly follow-up for a minimum of 24 months, with yearly follow-up thereafter up to 60 months or until progression. In case of clinical progression, the patient will be treated according to the EAU guidelines

(h) In case of SBRT/WPRT, PSA has to be determined on the day of the last fraction. In case of sLND in arm A, PSA will be determined at 4 weeks after surgery (follow-up month 1). In case of sLND + WPRT in arm B, PSA will be determined at 4 weeks post-WPRT (follow-up month 1)

(i) At time of primary endpoint is reached, a new biomarker sampling is preferred, but optional

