SBRT (MDT):A total dose of 30 Gy (80% of the maximal dose) will be delivered in 3 fractions and fractions will be separated > 48 h and < 96 h. Treatment will be prescribed to the periphery of the target (80% of the dose (= 30 Gy), should cover 90% of the PTV). In case of violation of dose constraints to the surrounding OAR, the prescription will be adapted accordingly.

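### For men with prior prostatectomy, biochemical PFS has two rules that disagree when PSA is above 0.20 ng/mL but still falling

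*Protocol article*

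**What the plan says.** In the Protocol article, Secondary endpoints, the clock for biochemical PFS is defined as: "Biochemical PFS: time between randomization and the day of the first recorded biochemical progression (as defined below), clinical progression or death due to clinical progression". Two PSA rules for men with prior prostatectomy follow.

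- **General rule:** "biochemical recurrence = PSA > 0.20 ng/mL, confirmed 2 weeks later". No earliest date, earlier fall or rise is required.
- **Non-responder rule:** men whose PSA has not dropped below 0.20 ng/mL "at time of first response assessment at 3 months follow-up, are considered as non-responders to treatment". They count as recurrent only "in case a second measurement at least 2 weeks later confirms a stable or rising PSA above this level".

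PSA is drawn before month 3. Table 1 lists it at the end of treatment and at month 1. Note (h) adds: "In case of SBRT/WPRT, PSA has to be determined on the day of the last fraction". For sLND the first value is taken 4 weeks after surgery in arm A, and 4 weeks after WPRT in arm B.

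**The concern.** The inclusion criteria admit men in biochemical relapse, and the non-responder rule presumes a starting PSA above 0.20 that has to come down. The general rule therefore describes the state in which these men enter. Since the clock runs from randomization to the first recorded progression, a PSA that is falling on ADT but has not yet cleared 0.20 can be dated as an event.

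At stake is a named secondary endpoint. Early events that reflect only the entry condition would dilute it. If they fall unequally between arms, they would also distort the comparison. The trial is open-label and multicentre with no on-site quality control, so sites could apply the two rules differently.

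**Working it through.** **1. The rules side by side (prior prostatectomy)**

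| PSA course | General rule | Non-responder rule |
|---|---|---|
| 0.30 at month 3, repeat 0.25 | event (both above 0.20) | no event (repeat is falling) |
| 0.30 at month 3, repeat no lower | event | event |
| 2.0 at entry, 1.2 at last fraction, 0.6 two weeks later | event before month 3 | not yet assessed |
| below 0.20, later confirmed above 0.20 | event | does not apply |

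Rows 1 and 3 are the problem, and row 1 needs no assumption about kinetics. The rule for men with prior prostate radiotherapy is nadir plus 2 ng/mL, which a steadily falling PSA cannot meet.

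**2. Days on ADT at the first PSA after randomization**

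Inputs:
- SBRT: three fractions, and "fractions will be separated > 48 h and < 96 h".
- WPRT: 25 fractions, five per week (Radiotherapy).
- ADT lead before radiotherapy: 0 to 14 days (Table 1 note (a)).
- ADT after sLND: from day 1 to day 10.
- WPRT after sLND: from week 4 to week 12.

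Results:
- Arm A, SBRT: 2 × 2 = 4 to 2 × 4 = 8 days of treatment. With the lead, 4 + 0 = **4** to 8 + 14 = **22**.
- Arm B, WPRT with boost: 4 × 7 + 4 = 32 days from a Monday start. With the lead, **32** to 32 + 14 = **46**.
- Arm A, sLND: 28 − 10 = **18** to 28 − 1 = **27**.
- Arm B, sLND then WPRT: 28 + 32 + 28 − 10 = **78** to 84 + 32 + 28 − 1 = **143**.
- Arm A, SBRT combined with prostate-bed radiotherapy in 33 fractions: 6 × 7 + 2 = 44 days. With the lead, **44** to **58**.

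The Androgen deprivation therapy section gives a lead of at most one week, not two. The passages need reconciling. With 7 days the ranges become 4 to 15 (SBRT) and 32 to 39 (WPRT), and the order is unchanged.

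**3. Illustration under assumed kinetics**

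The document gives no PSA kinetics. Assume PSA(t) = P0 × 0.5^(t/h) from ADT start, with P0 = 2.0 ng/mL and a half-life h of 1, 2 or 3 weeks. Cells show first value / confirming value; a literal event needs both above 0.20.

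| Timing (weeks on ADT) | h = 1 | h = 2 | h = 3 | Events |
|---|---|---|---|---|
| Arm A SBRT, 1 and 3 | 1.00 / 0.25 | 1.41 / 0.71 | 1.59 / 1.00 | 3 of 3 |
| Arm A SBRT, confirmed at month 1: 1 and 5 | 1.00 / 0.06 | 1.41 / 0.35 | 1.59 / 0.63 | 2 of 3 |
| Arm A SBRT, 2-week lead: 3 and 5 | 0.25 / 0.06 | 0.71 / 0.35 | 1.00 / 0.63 | 2 of 3 |
| Arm B WPRT, 5 and 7 | 0.06 / 0.02 | 0.35 / 0.18 | 0.63 / 0.40 | 1 of 3 |
| Arm B WPRT, confirmed at month 1: 5 and 9 | 0.06 / 0.004 | 0.35 / 0.09 | 0.63 / 0.25 | 1 of 3 |
| Arm B WPRT, 2-week lead: 7 and 9 | 0.02 / 0.004 | 0.18 / 0.09 | 0.40 / 0.25 | 1 of 3 |

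A wider grid used P0 of 0.5, 1, 2 and 5 ng/mL and h of 7, 14, 21 and 28 days (16 cells), with a repeat after 14 days. Cells with a literal event:
- Arm A SBRT: 13 at ADT day 8, 9 at day 22.
- Arm A sLND: 9 at day 22.
- Arm B WPRT: 8 at day 32, 6 at day 46.
- Month 3: 1 in arm A SBRT (day 99), 0 in arm B (day 123).

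**4. Sample size**

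The planned 178 patients rest on MFS alone. Schoenfeld's formula with hazard ratio 24/36, two-sided alpha 0.20 and 80% power gives 110 events. At an average event probability of 0.659 that is 167 patients, or 176 after 5% loss. Freedman's formula gives 182. The figure reproduces and does not depend on this point.

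**The case against.** The section can be read coherently. It calls month 3 the first response assessment, and recurrence suggests a man who had first responded. If the general rule ran from randomization, the non-responder rule would be redundant for these men, since a confirmed stable or rising PSA above 0.20 already meets the general rule. This reading is plausible and probably intended, but it is not written down. A missing start date alone might be left to the full protocol. The conflict is different, because both rules are printed here.

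A reader might infer that false events arise mainly in an SBRT arm, or in every arm A patient. The documents do not support that:

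- There is no SBRT arm. Arm A is sLND or SBRT, and arm B patients can meet the general rule too.
- Three of three in arm A holds only with no ADT lead and a 2-week repeat that Table 1 does not schedule.
- Prostate-bed radiotherapy is highly recommended at PSA of 2 ng/mL or more, and for some pathology, so the 2.0 example fits SBRT alone only loosely. Bed radiotherapy moves the last fraction to about day 44 or later in arm A. In arm B it is combined with WPRT, so its 33 fractions end at a similar time. For such men the gap closes, or reverses if bed treatment follows SBRT.
- The direct month-3 conflict is rare under the assumed kinetics.

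A reader might also infer that MFS is biased. Biochemical progression does trigger restaging, but Follow-up asks for a PSA of at least 0.50 ng/mL before PET is considered, and an MFS event needs M1 disease or death. The gate limits this route without closing it: a PSA of 1.2 then 0.6 passes.

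**Conclusion.** The two rules contradict each other for a man with prior prostatectomy whose PSA is above 0.20 and falling. That is certain from the text. That the general rule is already met at entry is an inference from the required biochemical relapse and the non-responder wording, because the numerical entry threshold is not printed.

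False events are possible in both arms. An excess in arm A is likely, since both MDT strata point that way, and it should be largest for SBRT without prostate-bed radiotherapy. Its size depends on PSA kinetics, baseline PSA and case mix that the document does not give; the cell counts above are illustrations, not estimates. The point should be corrected, but it concerns a secondary endpoint. The sample size stands, and any effect on MFS is indirect and limited.

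**What to change.** Reconcile the rules in the definition of biochemical PFS. For men with prior prostatectomy, state that:

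1. no biochemical progression is called before the 3-month response assessment;
2. a man whose PSA has not yet fallen below 0.20 ng/mL is judged only by the non-responder rule (confirmed stable or rising), and this continues at later visits until he falls below 0.20 or has an event;
3. the general rule applies only after PSA has first fallen below 0.20 ng/mL.

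This is a counting rule for the endpoint. It costs a few sentences and adds no visit. The event date can be derived from the PSA values the trial already collects, including the repeat measurement that the non-responder rule already requires.

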***WPRT or SBRT:***
Physical examination at the end of treatmentAcute toxicity assessment (once a week for WPRT; for SBRT at the end of treatment): the highest grade of adverse events during radiotherapy will be reported at the end of treatment.Concomitant medicationTreatment planningRecord planning results

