### Follow-up

Follow-up is planned at month 1, 3 and 6 following treatment completion, 6-monthly thereafter until month 24 and then yearly up to month 60. Patients who withdraw from trial treatment in the absence of progression should continue to have follow-up visits as defined above. The following investigations should be performed at every follow-up visit (Table 1):
Clinical examination with late toxicity scoringPSA and testosterone measurementQoL-scoringPET-imaging only at time of biochemical progression or symptomatic progression and then 6-monthly thereafter until clinical progression is determined. In case of biochemical progression, the PSA should at least be 0.50 ng/mL before a new PET-CT scan should be considered. The location of progression should be recorded.At time of primary endpoint is reached, a new biomarker sampling is preferred, but optional.Concomitant medicationSurvival status

In case of clinical disease progression the patient will be treated according to each centre policy, but adherence to the EAU guidelines [24] is recommended. In case of local or regional oligometastatic recurrence during follow-up, a new MDT is allowed (this treatment falls outside the scope of this protocol).

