Although sLND is not a pure lesion-directed approach, the recurrence patterns of both SBRT and sLND are comparable with > 60% of patients relapsing in adjacent lymph node regions [11–13]. This might be explained by the fact that even the most extended sLND does not cover all potential pelvic lymph node metastasis landing sites. In a previous paper from our group, we indicated that an extended sLND technique only covers around 50% of these sites [41]. Consequently, we hypothesize that a larger RT field covering the elective nodal regions in a treatment field may be a more effective alternative to focal strategies. This is supported by a retrospective study by Rischke et al. [12], indicating a reduced pelvic lymph node recurrence rate following sLND plus WPRT as compared to sLND alone. On the other hand, compared to MDT strategies, longer OTT, higher toxicity rates and limited re-treatment possibilities are expected by delivering elective nodal irradiation. Nevertheless, WPRT grade 3 toxicity rates appear to be low in recent trials such as OLIGOPELVIS and SPPORT [42, 43].

In both arms, short term ADT will be mandatory. The rationale for the use of temporary ADT is extrapolated from the data in the salvage setting (GETUG16, RTOG9601, SPPORT, OLIGOPELVIS), indicating that temporary ADT reduces the rate of biochemical and clinical recurrences [12, 18, 19, 42, 43]. There are no clear guidelines on the ideal duration of ADT in this setting, so we opted for 6 months as studied in GETUG16, OLIGOPELVIS and SPPORT [19, 42, 43].

As no direct comparison of the two approaches have been made to date, prospective studies using well-defined endpoints and predefined treatment approaches are therefore needed to validate the best treatment approach in the nodal oligorecurrent setting. The STORM study will be the first prospective multicentre randomized controlled phase II trial to assess the possibility of prolonging the MFS by adding WPRT to either sLND or SBRT, both in combination with short-term ADT in PCa patients with nodal oligorecurrent disease.

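### CTCAE is tied to radiotherapy-attributed toxicity, so arm A men with salvage dissection and no prostate-bed radiotherapy have no defined GI, rectal or urinary grade at the visits both arms share

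*Protocol article*

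**What the plan says.** Scale and timing are set by treatment modality.

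- **Scale.** Secondary endpoints: "Acute and late toxicity due to radiotherapy will be assessed according to the National Cancer Institute Common Terminology Criteria for Adverse Events", with rectal, gastrointestinal and urinary events singled out. For surgery, intra-operative problems and "post-operative surgical complications will be scored using the Clavien-Dindo Classification of Surgical Complications".
- **During treatment.** Table 1, footnote (f): "During the treatment period a toxicity assessment should be done at least once a week in case of WPRT". The same footnote continues: "For SBRT toxicity assessment should be done only at end of treatment, for sLND at discharge (Clavien-Dindo scale". Under Evaluation during treatment, for WPRT and SBRT alike, "the highest grade of adverse events during radiotherapy will be reported at the end of treatment".
- **After treatment.** "Follow-up is planned at month 1, 3 and 6 following treatment completion, 6-monthly thereafter until month 24 and then yearly up to month 60". Table 1 has a baseline toxicity entry, acute toxicity at end of treatment and months 1 and 3, and late toxicity from month 6, for all patients. The Follow-up section asks for toxicity scoring at each visit. Neither place names a scale.
- **Acute window.** "Acute toxicity: occurring during and up to 3 months after treatment completion".
- **Context.** The Randomization section says the trial is open label. The Discussion says that with elective nodal irradiation "longer OTT, higher toxicity rates and limited re-treatment possibilities are expected".

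**The concern.** WPRT is given only in arm B and SBRT only in arm A, so rules written by modality partly become differences between the randomized groups. The clearest case is the sLND stratum. The same urinary symptom at month 12 would receive a CTCAE grade in an arm B man if judged to come from radiotherapy. It would have no defined grade in an arm A man who had surgery alone.

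The trial is meant to inform whether WPRT goes on to phase III, and the Discussion itself names higher toxicity as an expected cost. A later analysis can choose how to summarize grades, but it cannot recover grades that were never collected.

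**Working it through.** The plan gives no figure for toxicity, so there is none to reproduce. Its one sample size, 178, is for metastasis-free survival and is used here only to get 178 / 2 = 89 men per arm.

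**1. Who has a CTCAE grade under the wording**

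| Group | Clavien-Dindo at discharge | CTCAE defined |
|---|---|---|
| Arm A, SBRT | not applicable | yes |
| Arm B, WPRT with boost | not applicable | yes |
| Arm A, sLND, no prostate-bed radiotherapy | yes | no |
| Arm A, sLND with prostate-bed radiotherapy | yes | yes |
| Arm B, sLND then WPRT | yes | yes |

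The gap is the third row. It covers late as well as acute toxicity, because both are defined through radiotherapy. The Surgery section adds that WPRT is not given in arm B if surgical morbidity prevents a safe start. Those men would also have no CTCAE grade, although they are analysed in arm B.

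**2. How many men**

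The document gives neither the sLND share nor the share receiving prostate-bed radiotherapy. Assume an sLND share of 20%, 35% or 50% of arm A:

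- 89 × 0.20 = 18
- 89 × 0.35 = 31
- 89 × 0.50 = 44 (rounded down from 44.5)

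These are upper limits, since some of these men will have prostate-bed radiotherapy.

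**3. On-treatment assessments in the SBRT stratum**

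- WPRT: 25 fractions at 5 per week = 5 weeks, so at least 5 assessments.
- SBRT: 3 fractions with two gaps of 48 to 96 hours = about 4 to 8 days, with 1 assessment.

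Per week of treatment the intensity is similar. What differs is the number of assessments feeding the highest grade.

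**4. Can the effect of step 3 be sized?**

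Only by assumption. If each assessment independently records an event with chance q, the chance of at least one in k assessments is 1 − (1 − q)^k. With q = 0.05:

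- On treatment only: k = 1 gives 5%, and k = 5 gives 1 − 0.95^5 = 23%.
- Whole acute window, adding the shared visits at months 1 and 3: k = 3 gives 1 − 0.95^3 = 14%, and k = 7 gives 1 − 0.95^7 = 30%.

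The ratio falls from about 4.5 to about 2 simply by counting the shared visits. Both are upper-bound illustrations: grades within one man are likely to be correlated, an end-of-treatment score can include recall, and some of the excess is real exposure time. No bias estimate follows from the document.

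**5. Attribution**

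For irradiated men in both arms, an event enters the CTCAE endpoint only if it is judged to come from radiotherapy. The article does not say who makes that judgement, and treatment is known. This could push the comparison either way.

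**The case against.** The other side has a good deal to say.

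- Scales follow modality, not arm. sLND occurs in both arms with the same Clavien-Dindo score at discharge, SBRT and WPRT share CTCAE, and type of metastasis-directed therapy is a stratification factor. This stands. Clavien-Dindo for surgery is not a fault.
- A reader might infer that arm A scores zero on CTCAE by construction throughout the sLND stratum. The document does not support that. The Interventions section allows prostate-bed radiotherapy after sLND in arm A and highly recommends it for defined groups. The gap is confined to sLND men who do not have it.
- A reader might take 23% against 5% as the bias from weekly scoring. It is not, for the reasons in step 4. In addition, the highest-grade rule applies to SBRT as well as WPRT, so the one SBRT score is meant to cover its whole short course.
- Common visits already exist, and late visits follow the same schedule in both arms. Assessment frequency therefore cannot distort late toxicity. Quality-of-life questionnaires are also collected on one schedule in all men. This stands.
- No between-arm toxicity test and no toxicity criterion for phase III is stated, and an article condenses a fuller protocol. This limits the weight of the point. It does not remove it: the restriction to radiotherapy-attributed events is a rule the article states, not a detail it leaves out.

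**Conclusion.** The concern holds in a limited form. As worded, CTCAE GI, rectal and urinary grades are undefined for arm A men treated with sLND and no prostate-bed radiotherapy, for acute and late toxicity, while arm B sLND men who receive WPRT have them. That tilts the recorded harm against WPRT in this stratum. Attribution in an open-label trial adds a filter of unknown direction. In the SBRT stratum, at least five on-treatment assessments against one makes on-treatment acute capture unequal, but part of that is genuine exposure time and late toxicity is untouched.

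The size is not derivable. The range of 18 to 44 men rests on an assumed sLND share of 20% to 50% and is an upper limit. A reader might go further and conclude that the harm comparison cannot be interpreted at all. The document does not support this: most of the schedule is shared, and irradiated men in both arms are scored on CTCAE. The point is a cheap improvement to a secondary endpoint and has no bearing on the sample size.

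**What to change.** In Secondary endpoints and Table 1, state that CTCAE v4.0 gastrointestinal, rectal and urinary items are scored in every man, regardless of cause or treatment modality, at baseline, end of treatment, months 1, 3 and 6, and every later visit. State that the main between-arm toxicity summary uses these common visits. Continue to report the weekly on-treatment WPRT maxima, noting the different number of assessments, and the Clavien-Dindo grades alongside. Attribution to radiotherapy can still be recorded as a separate item.

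The cost is wording plus one CTCAE form for sLND-only men at visits that already take place. There are two limits. The common-visit summary will miss some transient on-treatment events, which is why the weekly maxima must still be shown. The visits are also counted from treatment completion, which in arm B sLND men falls about 4 + 5 = 9 to 12 + 5 = 17 weeks after surgery. The tables should therefore make the time origin clear.

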The gross target volume (GTV) will be defined as all known gross disease before any treatment, defined by CT/MRI/PET-CT images and/or clinical information. A GTV_PB may be defined with the help of MRI and PET imaging.The CTV will encompass regions at risk of microscopic extension. For CTV_PB, consensus guidelines such as EORTC, RTOG or FROGG are being followed [29–31]. The CTV_LNN consists of the pelvic lymph node regions as described in the RTOG guidelines [31], with the exception that delineation of the common iliac lymph nodes should start at the L4/L5 interspace [32] and should encompass the GTVs. No CTV is mandatory for SBRT.The PTV (PTV_PB, PTV_SBRT and PTV_LNN) will provide margin around the CTV to compensate for variability in daily treatment set-up and internal CTV motion due to breathing or motion during treatment. PTV_PB is created by a 5 to 10 mm margin for centres with or without image-guided radiotherapy, respectively. The PTV_LNN must include the entire CTV_LNN plus a minimum 3D-margin of 5 mm. For the nodal GTVs located within CTV_LNN, a margin of 5 mm is used. The PTV_SBRT should encompass the GTV with a minimal margin of 3 mm in all directions.
4.Dose prescription:Intensity modulated radiotherapy (IMRT) or use of rotational techniques is mandatory in case of WPRT and SBRT. In case of SBRT, treatment with Cyberknife® is allowed. 3D conformal technique is not allowed in this trial.
WPRT or PB-RT:All fields and the entire PTV_LNN must be treated daily for 5 days per week in a once-daily schedule of 1.8 Gy per fraction, for a total dose of 45 Gy in 25 fractions. The GTV should receive an integrated boost to a median dose of 65 Gy in 25 fractions, 2.6 Gy per fraction. If a suspicious node is still present following sLND, it is allowed to boost the GTV to the same dose during WPRT. In case of PB-RT, the PTV_PB should receive at least 66 Gy in 33 fractions.

Normalization of the treatment plan will cover 95% of the PTV_LNN or PTV_PB with the prescription dose. Furthermore, 98% of the PTV_LNN or PTV_PB should receive 95% of the prescription dose with 2% of the PTV not exceeding 107% of the prescribed dose.

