#### Surgery – sLND (MDT)

A bilateral extended lymph node dissection of the true pelvis will be performed either via an open or minimally invasive approach, which is at the discretion and expertise of the surgeon. A minimally invasive technique is preferred, but not mandatory. In case of pelvic nodal uptake, all nodal/fibrofatty tissue at the external and internal iliac regions and obturator fossa region will be removed. For pelvic nodal metastases, in case of a previous extended lymphadenectomy, only the suspicious lymph node(s) will be removed. The definition of the true pelvis is defined according to the AJCC Cancer Staging Manual 7th edition and the regions are defined by Mattei et al. [33]. An extended lymph node dissection of regions I and II is recommended in this study.

In case of WPRT after sLND in arm B: WPRT should start between the 4th and 12th week following sLND. In case the morbidity of sLND does not allow a safe start of RT in this period, radiotherapy will not be carried out.

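### The acute/late toxicity split at 3 months after treatment completion suits radiotherapy toxicity, but is not a like-for-like basis for comparing harm between arms in the sLND stratum

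*Protocol article*

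**What the plan says.** The Secondary endpoints section divides toxicity by time. The early part is "Acute toxicity: occurring during and up to 3 months after treatment completion" and the later part is "Late toxicity: occurring later than 3 months after treatment completion". The item that carries these two lines begins "Acute and late toxicity due to radiotherapy will be assessed according to the National Cancer Institute Common Terminology Criteria for Adverse Events". It puts surgery on a scale of its own: "post-operative surgical complications will be scored using the Clavien-Dindo Classification of Surgical Complications".

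Table 1 note (b) fixes when treatment is complete: "Treatment period is defined as the time between first treatment day and last treatment of surgery and/or radiotherapy". The 6 months of ADT do not count towards it. For arm B after surgery, the sLND section says "WPRT should start between the 4th and 12th week following sLND". The Radiotherapy section has the pelvic volume "treated daily for 5 days per week in a once-daily schedule of 1.8 Gy per fraction", with 25 fractions in all.

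Table 1 has one acute row (end of treatment, months 1 and 3) and one late row (month 6 onwards). Neither is limited to one arm or to irradiated patients. Note (f), attached to the acute row, includes the sLND scoring at discharge. The Follow-up section counts visits from treatment completion in both arms, and asks for late toxicity to be scored at every visit.

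**The concern.** Added harm is what any gain in MFS has to be weighed against. The Discussion expects more toxicity with WPRT, and the Sample size section says the trial is to show whether the experimental arm merits a phase III trial.

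An sLND patient in arm A completes treatment on the day of surgery. An sLND patient in arm B completes it only after the wait for WPRT and the WPRT course. With the cut set at 3 months after completion, the two acute windows differ in length, and the same calendar time after surgery can fall on different sides of the cut. Side-by-side acute and late rates in this stratum would then partly reflect time at risk and labelling as well as the effect of WPRT.

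**Working it through.** The plan states no window length, so there is no figure of its own to reproduce. The lengths follow from its definitions.

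**Inputs**
- Acute window: first treatment day to 3 months after completion (Secondary endpoints; Table 1 note b).
- Wait from sLND to WPRT: 4 to 12 weeks (sLND section).
- WPRT: 25 fractions at 5 per week, about 5 weeks if uninterrupted (Radiotherapy).
- SBRT: 3 fractions with two gaps of more than 48 h and less than 96 h, about 4 to 8 days in all (Radiotherapy).
- Conversion: 4.348 weeks per month.

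**Formula:** acute window in months = (weeks from first to last treatment) / 4.348 + 3.

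| Stratum | Arm A | Arm B |
|---|---|---|
| sLND, no prostate-bed RT | 0 / 4.348 + 3 = 3.0 | (4 + 5) / 4.348 + 3 = 5.1, up to (12 + 5) / 4.348 + 3 = 6.9 |
| SBRT, no prostate-bed RT | 3.1 to 3.3 | 5 / 4.348 + 3 = 4.15 |

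**Sensitivity.** Counting the 4th week from its first day and WPRT as 4 weeks and 4 days lowers the arm B sLND minimum to (3 + 4.57) / 4.348 + 3 = 4.7 months. With 33 prostate-bed fractions (6 weeks and 3 days) given alongside WPRT, the arm B sLND range is 5.4 to 7.2 months. Prostate-bed RT after sLND in arm A gives 6.43 / 4.348 + 3 = 4.5 months plus the wait before it starts, which the article does not state.

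**What this does to labels.** The month-3 visit of an arm B sLND patient falls 5.1 to 6.9 months after surgery and is scored acute. The month-6 visit of an arm A sLND patient falls 6 months after surgery and is scored late. ADT starts 1 to 10 days after sLND in both arms and runs for 6 months. The arm A acute window covers about half of that course, and the arm B window most or all of it.

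**Illustration, on assumed rates.** Take a constant monthly hazard h, equal in both arms, of an event unrelated to radiotherapy. The proportion classed acute is 1 − exp(−h × window).

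| Assumed h per month | Arm A, 3.0 months | Arm B, 5.1 to 6.9 months |
|---|---|---|
| 1% | 3.0% | 4.9% to 6.7% |
| 2% | 5.8% | 9.6% to 12.9% |
| 4% | 11.3% | 18.4% to 24.1% |

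The hazards are not from the documents, and surgical complications would not plausibly arise at a constant rate. The table shows the direction and rough scale of the effect for events counted under the split, not an expected result.

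**The case against.** The strongest reply is that the split belongs to an item on radiotherapy toxicity, with surgical morbidity on the Clavien-Dindo scale. A patient who has sLND alone receives no radiotherapy, so he has no radiotherapy toxicity to misplace. Every irradiated patient has the same 3 months after his last fraction. For that toxicity the anchor is even-handed, and the longer treatment phase in arm B is part of the intervention. This stands. A reader might infer that acute and late rates differ between arms by construction; the documents do not support so broad a claim.

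Three further limits also stand:
- Prostate-bed RT, which the Interventions section highly recommends for defined groups, lengthens the arm A window. Where it is combined with SBRT in arm A and with WPRT in arm B, both windows are about 4.5 months. The 3 versus 5-to-7-month contrast therefore applies to a subgroup whose size is not given.
- An arm B patient whose surgical morbidity prevents WPRT keeps a 3-month window.
- The Data analysis section specifies no between-arm test of acute or late rates, so no faulty comparison has been laid down.

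What the reply does not settle is scope. Table 1 schedules acute and late scoring for all patients and places the sLND assessment under its acute row. If only radiotherapy-attributed events count, sLND patients in arm A without prostate-bed RT have no comparable toxicity measure. Attribution would also be a judgement made in an open-label trial. If all events count, the labels shift by arm as shown above.

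The late-scoring phrase in the Follow-up section is a wording slip. The same sentence refers to Table 1, which agrees with the endpoint definitions. It lends no weight to the window argument.

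**Conclusion.** The point holds in a narrow form. Among sLND patients without prostate-bed RT who receive their assigned treatment, the acute window is about 3 months in arm A and about 5 to 7 months in arm B. ADT-related, surgical or background events roughly 3 to 7 months after sLND can take different labels by arm if they are counted under the split. In the SBRT stratum the difference is about 1 month and matters little. The figures assume an uninterrupted 5-week WPRT course.

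This concerns a secondary endpoint and does not touch the MFS analysis. It is worth acting on because the remedy costs almost nothing and the comparison of harm matters to the phase III decision.

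**What to change.** - Keep the split at 3 months after completion as a description of radiotherapy toxicity.
- For the comparison between arms, also report worst grade and cumulative incidence of grade 2+ and 3+ CTCAE events, whatever their attribution, over common windows from randomisation, for example 0-6 months, 6-24 months and overall.
- Choose the first boundary with the schedule in view. Treatment may start up to 8 weeks after randomisation, so sLND plus WPRT can end as late as (8 + 12 + 5) / 4.348 = 5.7 months. The overall window should therefore be reported as well as the early one.
- Reconcile the Follow-up wording on late scoring at every visit with the endpoint definitions and Table 1.

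The cost is one extra set of tables and a few sentences, with no extra visits. It assumes that event onset dates are recorded, which the article does not state. Common windows equalise time at risk but not the number of assessments, since WPRT patients are scored weekly during treatment; the report should say so.
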